## Abstract

**Background:**

Patients with reduced responsiveness to clopidogrel often have diminished platelet inhibition, a factor associated with increased rates of major adverse cardiovascular events. Clinical trials that have focused on reducing high on-treatment platelet reactivity (HPR) with an additional loading dose of clopidogrel have reported varying effects. Prasugrel, a newer thienopyridine, exhibits a more consistent antiplatelet effect and more rapid onset time when compared to clopidogrel. We hypothesize that prasugrel reloading would be more effective than clopidogrel reloading in patients with HPR after an initial loading dose of clopidogrel.

**Method/Design:**

Comparison of Prasugrel and Clopidogrel Reloading on High Platelet Reactivity in Clopidogrel-loaded Patients Undergoing Percutaneous Coronary Intervention (PRAISE-HPR) is a prospective, randomized, open-label, active controlled study. A total of 76 patients undergoing percutaneous coronary intervention (PCI), with HPR after administration of a loading dose of clopidogrel will be randomly assigned to either prasugrel or clopidogrel groups, and patients in each group will be reloaded with 20 mg of prasugrel or 300 mg of clopidogrel. The primary endpoint will be HPR at 24 hours after PCI, as determined by the VerifyNow assay during the study period. The rate of sustained high platelet reactivity and 30-day clinical outcomes will also be measured.

**Discussion:**

PRAISE-HPR is a randomized controlled clinical trial to investigate the efficacy and safety of reloading prasugrel and clopidogrel in suppressing residual high platelet reactivity. The results will be made publicly available in the year 2013.

**Trial registration:**

NCT01609647

## Background

In patients with acute coronary syndrome (ACS) who undergo percutaneous coronary interventions (PCI), common recommendations for antithrombotic regimens include dual antiplatelet therapy with aspirin and clopidogrel [1,2]. Clopidogrel is a thienopyridine derivative metabolized by cytochrome P450 to an active metabolite that irreversibly inhibits platelet P2Y_12_ receptors [3]. Although the efficacy of clopidogrel has been well established, it exhibits pharmacodynamic variability in diverse conditions which can be due to the loss-of-function *CYP2C19* allele, drug-drug interactions or clinical factors [4]. High on-treatment platelet reactivity (HPR) after clopidogrel administration is associated with adverse cardiovascular events [5-11] and the rate of HPR can be reduced with either a higher loading dose (LD) or maintenance doses (MD) of clopidogrel, or a potent alternative drug [2,12-14]. The use of double doses of clopidogrel and the more potent thienopyridine prasugrel to reduce HPR and subsequent cardiovascular events have not been successful, partially due to the studies being conducted with low event rates and low-risk patients [15,16]. Another issue concerning prior study design has been the delayed administration of drugs, administered after PCI in both cases. Therefore, a platelet reactivity (PR) guided trial with reloading of a more potent drug in the early phase of ACS, especially before PCI, is warranted.

Prasugrel is also a thienopyridine derivative. However, the metabolism of prasugrel is much more efficient than that of clopidogrel, because it occurs via esterases and has less dependency on cytochrome P450 enzymes [17]. As a result, prasugrel treatment results in more rapid onset, more consistent conversion from the inactive prodrug to active metabolite, and higher blood concentrations of the active metabolite [18]. A LD of prasugrel 60 mg results in more rapid, potent and consistent inhibition of platelet function than clopidogrel LDs of 300 mg or 600 mg [19].

We hypothesize that for patients with HPR after an initial LD of clopidogrel, reloading with prasugrel in the early phase of ACS will reduce PR more effectively than reloading with clopidogrel, resulting in a reduction of adverse cardiovascular events.

## Methods and design

### Trial objectives

The primary aim of this study is to compare PR if 20 mg of prasugrel is reloaded, followed by MDs of 5 mg daily, versus clopidogrel reloading with 300 mg followed by MDs of 75mg per day, prior to PCI in ACS patients with HPR after an initial LD of clopidogrel.

### Study design

PRAISE-HPR is a prospective, randomized, open-label, active controlled study with two parallel study groups. It will be conducted at Dong-A University Hospital in Busan, Republic of Korea. Participants will be randomly allocated into prasugrel or clopidogrel reloading groups. Clinical endpoints will be measured at four weeks post-procedure. Recruitment of participants began in November 2012. The overall study design is depicted in Figure 1. Study approval was granted by the Institutional Review Board (IRB) of Dong-A University Hospital, and consecutive, eligible patients will be required to provide written informed consent.

**Figure 1 F1:**
[figure not shown]
**Overall study design. **ACS, acute coronary syndrome; UA, unstable angina; NSTEMI, myocardial infarction without ST-segment elevation; PCI, percutaneous coronary intervention; PR, platelet reactivity; MI, myocardial infarction.

### Randomization

Random treatment assignments will be generated using Excel spreadsheet software (Microsoft Corporation, Redmont, DC, USA). Eligible patients will be randomly assigned, on a 1:1 ratio, to receive reloading with either prasugrel or clopidogrel. Treatment randomization will be performed by independent personnel not involved in the study.

### Approval

This study will be conducted according to principles outlined in the Declaration of Helsinki. All patients must provide written informed consent, understanding that participation is voluntary and can be withdrawn at any time without any negative consequences concerning their current or future medical treatment. This study protocol has been approved by the IRB of Dong-A University Hospital.

### Patient population

Male and female patients, aged between 20 and 80 years for which the decision to undergo PCI within 24 hours has been made, due to ACS without ST-segment elevation are eligible for the study (Table 1).

**Table 1 T1:** Eligibility criteria

**Inclusion criteria**	**Exclusion criteria**
Subjects 20 to 80 years old	Body weight < 50 kg
Male or female gender	Contraindications for study drugs
ACS without ST-segment elevation	Urgent PCI for ACS
Planned to undergo PCI	Use of glycoprotein IIb/IIIa inhibitor
Patients who provided written informed consent	History of transient ischemic attack
	Active internal bleeding or bleeding diathesis
	Upper gastrointestinal bleeding in the past six months
	Hemoglobin < 10 g/dl or platelets < 100,000/mm^3^
	Renal dysfunction (serum creatinine > 2.5 mg/dl)
	Hepatic dysfunction (serum transaminase > three times normal limit)

ACS, acute coronary syndrome; PCI, percutaneous coronary intervention.

Patients requiring urgent PCI for ACS will be excluded from entry, as will those with recent or planned medical treatment with glycoprotein IIb/IIIa inhibitors, body weight < 50 kg, contraindication to the study drug, a history of transient ischemic attack, active internal or bleeding diathesis, hemoglobin < 10 g/dl, platelet count < 100,000/mm^3^, renal insufficiency with serum creatinine level > 2.5 mg/dl or significant hepatic dysfunction.

### Intervention and comparator descriptions

Before randomization, 300 mg of aspirin and 600 mg of clopidogrel will be administered as LDs according to the conventional guidelines for ACS [2]. For those who have already been receiving clopidogrel for five days or more, 300 mg of clopidogrel will be administered as a LD. PR will be evaluated before PCI and defined as the time between the arrival of the patient at the angiography room, and the beginning of coronary angiography. Angiography will not begin before confirmation of PRU. Patients who exhibit HPR defined as a PRU value of 240 units or more by VerifyNow (Accumetrics, San Diego, CA, USA) will be randomized and followed by assignment to either the clopidogrel reloading group (clopidogrel 300 mg) or the prasugrel reloading group (prasugrel 20 mg). Angiography in patients with HPR will begin after administration of the study drug. PR will be checked serially using the VerifyNow (Accumetrics, San Diego, CA, USA) assay at four hours, 24 hours and 30 days after PCI. Patients will be required to visit the outpatient clinic at Day 30 for measurement of PR. For patients discharged before Day 8, a secondary visit at Day 15 will be recommended.

In the clopidogrel reloading group, 300 mg clopidogrel will be reloaded, followed by MDs of clopidogrel 75 mg/day for 30 days. In the prasugrel reloading group, 20 mg of prasugrel will be reloaded, followed by prasugrel administration of 5 mg/day for 30 days.

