### Adverse effects

Patients will be interviewed daily during admission and at each visit after discharge regarding the occurrence of any adverse events, including time of onset, duration and severity. At each interview, patients will be assessed for reported bleeding classified by the TIMI bleeding classification scheme [20] as well as the BARC definition [21]. All information regarding adverse events will be to be presented on a case report form. The causal relation to the study drug and the intensity of adverse events will be evaluated by the investigators. Serious adverse events will be reported to the IRB and study sponsor by the principal investigator within 24 hours of being reported by the subjects or the treating physicians.

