## Discussion

Although clopidogrel is an effective antiplatelet agent, variability in patient response and potential high PR remains a major shortfall. To date, recent studies focusing on tailored antiplatelet therapy have not shown benefits. However, a study comparing the efficacy of prasugrel and clopidogrel in early reloading for the management of HPR after clopidogrel LD has not been conducted. In addition, guidelines for managing HPR before or during PCI in ACS patients have not documented.

Our current investigation into reloading prasugrel versus clopidogrel for reductions of HPR in ACS patients undergoing PCI is based on the hypothesis that prasugrel reloading is superior to clopidogrel for HPR and adverse event reduction, including periprocedural MI. Our protocol design has some safeguards to avoid performance and evaluation bias. Randomization will be performed with computer software. Data will be recorded and analyzed by specialists who are not aware of treatment allocation.

A major safety concern for this trial is an increased risk of bleeding. In TRITON-TIMI 38, higher rates of bleeding (particularly non-coronary artery bypass graft-related TIMI major bleeding) were observed in the prasugrel group [25]. However, in comparison to clopidogrel, prasugrel provided greater protection from ischemic events (particularly stent thrombosis, urgent revascularization and MI). We therefore anticipate that the benefit of antiplatelet efficacy will outweigh the increased risk of bleeding.

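### After discharge, bleeding is asked about only at visits, and only Day 30 is required, so scheduled enquiry and recall of minor bleeding vary with length of stay and optional attendance

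*Protocol article*

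**What the plan says.** Under Measurement of outcomes, bleeding by TIMI and BARC criteria is a secondary endpoint at 30 days. The Discussion gives it more weight: "A major safety concern for this trial is an increased risk of bleeding".

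The Adverse effects section sets out how bleeding is found: "Patients will be interviewed daily during admission and at each visit after discharge regarding the occurrence of any adverse events". It adds: "At each interview, patients will be assessed for reported bleeding classified by the TIMI bleeding classification scheme", with BARC alongside.

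The visits are fixed under Intervention and comparator descriptions. One is required of everyone: "Patients will be required to visit the outpatient clinic at Day 30 for measurement of PR". The other is conditional and optional: "For patients discharged before Day 8, a secondary visit at Day 15 will be recommended".

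On design: "PRAISE-HPR is a prospective, randomized, open-label, active controlled study with two parallel study groups".

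**The concern.** Bleeding is graded from what patients report when interviewed. Events that bring a patient to medical attention will usually surface anyway. Minor events, such as low-grade BARC bleeding, depend on being asked and on remembering.

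Under the stated schedule, how often a patient is asked and how far back they must remember depend on two things settled after randomisation: the length of the index stay, and whether an optional visit is attended. Neither is neutral. A bleed can prolong admission, and a patient who knows which drug they are taking may be more or less inclined to attend or to mention bruising.

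The Day 8 rule also leaves a gap of its own. A patient discharged on Day 7 is offered a Day 15 visit, while one discharged on Day 8 is offered nothing before Day 30.

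At stake are the completeness of the minor-bleeding data and, for patients who miss Day 30, whether there is any scheduled post-discharge enquiry at all.

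**Working it through.** The article gives no figure for ascertainment that could be reproduced, so the check is a count from the stated schedule.

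**Inputs.** Daily interviews to discharge and interviews at each later visit (Adverse effects). Day 30 required, and Day 15 recommended only if discharge is before Day 8 (Intervention and comparator descriptions). 76 randomised and a 20% allowance for follow-up loss (Sample size).

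**Assumptions.** The last in-hospital interview is on the day of discharge, L. There is one interview per day from Day 1 to Day L. All days are counted from the same origin.

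**Longest interval without a scheduled contact.** Without Day 15 it is 30 − L. With Day 15 it is the larger of 15 − L and 30 − 15 = 15. Interviews number L + 1 without Day 15 and L + 2 with it.

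| Discharge day | Day 15 visit | Interviews | Longest interval |
|---|---|---|---|
| 2 | attended | 4 | 15 days |
| 2 | skipped | 3 | 30 − 2 = 28 days |
| 7 | attended | 9 | 15 days |
| 7 | skipped | 8 | 30 − 7 = 23 days |
| 8 | not offered | 9 | 30 − 8 = 22 days |
| 14 | not offered | 15 | 30 − 14 = 16 days |

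The share of the 30 days under daily enquiry is 2/30 = 7% for discharge on Day 2 and 8/30 = 27% for discharge on Day 8.

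**What this does to recall.** A Day 15 contact shortens recall only for bleeds between discharge and Day 15. For example, a minor bleed on Day 3 in a patient discharged on Day 2 is first asked about 30 − 3 = 27 days later if Day 15 is skipped, and 15 − 3 = 12 days later if it takes place. Bleeds after Day 15 wait until Day 30 either way.

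**What this does to patients who miss Day 30.** The planning allowance of 20% is 0.20 × 76 = 15.2, about 15 patients. The article does not say how much of it falls at Day 30, so this shows only that attendance is not taken for granted. A patient who misses Day 30 and had no Day 15 visit has no scheduled enquiry after discharge. With a Day 15 contact, 15 − 2 = 13 of the 28 post-discharge days are covered after discharge on Day 2, and 15 − 8 = 7 of 22 after discharge on Day 8.

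**With Day 15 required for all.** Discharge up to Day 15 gives a longest interval of 15 days, and later discharge gives 30 − L, which is shorter. No interval exceeds 15 days.

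**The case against.** The strongest reply is that the plan already has a backstop. Every patient is required to attend at Day 30, and each interview asks about more than current symptoms: "Patients will be interviewed daily during admission and at each visit after discharge regarding the occurrence of any adverse events, including time of onset, duration". How severe the event was is asked as well. A Day 30 interview therefore covers the whole period. Serious events have a second route, since they go to the IRB and sponsor "within 24 hours of being reported by the subjects or the treating physicians", without waiting for a visit. This stands. A reader might infer that a patient bleeding at home is invisible to the trial for four weeks. The documents do not support that for serious bleeding. What is absent is a scheduled contact.

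The second reply is that both arms follow the same schedule. This also stands. Equal under-detection in both arms loses events but leaves their ratio unchanged. A patient kept in hospital by a bleed is already a case, so extra interviews add little to a comparison of patients with any bleed.

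A reader might still infer a distorted bleeding ratio. Suppose detection of a minor bleed is 0.9 with Day 15 attended and 0.6 without, and attendance is 80% in one arm and 60% in the other. Detection is then 0.8 × 0.9 + 0.2 × 0.6 = 0.84 against 0.6 × 0.9 + 0.4 × 0.6 = 0.78, a ratio of 1.08. Attendance of 90% against 40% gives 0.87/0.72 = 1.21. All these inputs are invented. The article gives no attendance, length-of-stay or bleeding rates and no sign of an arm difference. The sum also applies the loss to every minor bleed, although those in hospital or after Day 15 are unaffected by that visit. With 38 patients per arm and an assumed true risk of 10% to 30%, the 0.06 difference in detection is 0.06 × 3.8 = 0.2 to 0.06 × 11.4 = 0.7 of a patient. The ratios are not evidence of bias.

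Third, a journal article condenses the protocol, and interim telephone calls may be set out elsewhere. That is possible. However, the article does state the visit rule and ties bleeding enquiry to it, so the point rests on what is written. The statement in the Discussion that data are recorded and analysed by specialists unaware of allocation does not help here, because it cannot supply a contact that did not take place.

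**Conclusion.** The point holds as a modest weakness in ascertainment. It is not a contradiction in the plan, and the 24-hour primary endpoint is untouched. Scheduled enquiry about the trial's main safety concern varies with length of stay and optional attendance, with up to 28 days between scheduled contacts after discharge on Day 2 if Day 15 is skipped, and 22 days after discharge on Day 8.

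The likely consequences are under-recall of minor bleeding and lost data in patients who miss Day 30. Serious bleeding is largely protected. Bias in the comparison between arms is possible in an open-label trial, but only if stay, attendance or reporting differs by arm. Its direction and size cannot be calculated from the documents. The interval counts rest on the assumption that the last in-hospital interview falls on the day of discharge.

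**What to change.** Require one Day 15 safety contact, by telephone or in clinic, for every randomised patient whatever the discharge date. Use the same structured bleeding, adverse-event and MACE questions in both arms. This gives every patient the same minimum enquiry and keeps every interval without a scheduled contact to 15 days or less.

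Keep the daily in-hospital interviews and the Day 30 interview as part of the bleeding data. Restricting the comparison to fixed contacts would replace prospectively collected in-hospital records with recall, and could lose in-hospital bleeds in patients later lost to follow-up.

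The cost is one line in the visit schedule, at most 76 short calls and a little staff time. It would not remove reporting differences that arise because patients know their treatment.

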### Measurement of outcomes

The primary endpoint of this study will be HPR at 24 hours after PCI, as determined by the VerifyNow (Accumetrics, San Diego, CA, USA) assay during the study period (Table 2). The optimal cutoff value is defined as 240 units, as observed by Marcucci *et al*. [9]. Secondary endpoints include major adverse cardiovascular events at 30 days after PCI, including death from cardiovascular cause, myocardial infarction (MI), stent thrombosis, hemorrhagic or non-hemorrhagic stroke, and bleeding events defined by Thrombolysis in Myocardial Infarction (TIMI), as well as Bleeding Academic Research Consortium (BARC) criteria. HPR at four hours or 30 days after PCI will also be evaluated.

**Table 2 T2:** Primary and secondary outcomes

**Primary outcome**	**Secondary outcomes**
HPR (PR ≥ 240 units)	Death from cardiovascular cause
	Myocardial infarction
	Stent thrombosis
	Hemorrhagic or non-hemorrhagic stroke
	Target vessel revascularization
	Bleeding event defined by Thrombolysis in Myocardial Infarction (TIMI) criteria and BARC

HPR, high platelet reactivity: more than 240 units determined via VerifyNow (Accumetrics, San Diego, CA, USA); PR, platelet reactivity; BARC, bleeding academic research consortium.

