### Sample size

The sample size calculation is based on the primary outcome and the primary analysis for the intention-to-treat population. The sample size is calculated using the study’s primary objective to detect a 15% difference in PR suppression between reloading with prasugrel and clopidogrel, to a power of 80% to demonstrate difference. On the basis of previous reports we assume the inhibition of PR after a LD of clopidogrel to be approximately 55% of baseline [22]. The assumed inhibition of PR after LD of prasugrel is 70%. This was calculated from studies showing a 30% higher concentration of the active metabolite in patients of East Asian ethnicity [23] and an approximate 90% inhibition of baseline PRU two hours after a prasugrel 30 mg LD was given in healthy Korean people [24]. We expect the difference in PR inhibition will be at least 15% when considering ACS patients. We adjusted the sample size for an estimated follow-up loss rate of 20%, a two-sided level of significance of α = 5%, which determined that 38 patients in each group would be required to detect this difference with a two-sided Student’s *t* test. A total of 76 patients will be randomized and included in the analysis. We predict that 50% of patients will exhibit HPR as determined by VerifyNow (Accumetrics, San Diego, CA, USA) after receiving the clopidogrel LD. A total of 152 patients will be screened and 76 patients will be randomized and included in the analysis, with 38 patients in each group.

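### The aim and the sample size treat platelet reactivity as continuous, but the primary outcome keeps only HPR yes/no at 240 PRU, which discards the size of the fall and much of the power

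*Protocol article*

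**What the plan says.** Two parts of the Protocol article treat the outcome as continuous. Under Trial objectives: "The primary aim of this study is to compare PR if 20 mg of prasugrel is reloaded", against clopidogrel reloading. Under Sample size, the trial is sized to "detect a 15% difference in PR suppression between reloading with prasugrel and clopidogrel, to a power of 80% to demonstrate difference", with 55% inhibition assumed for clopidogrel and 70% for prasugrel, a two-sided t test, 20% loss to follow-up and 38 patients per group.

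Two other parts make it binary. Under Measurement of outcomes: "The primary endpoint of this study will be HPR at 24 hours after PCI, as determined by the VerifyNow" assay, and "The optimal cutoff value is defined as 240 units". Under Statistical analysis, the primary outcome goes into a logistic regression adjusted for clinically relevant imbalances at baseline. The covariates are not named, so entry PRU is neither required nor excluded.

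The entry rule uses the same number. Under Intervention and comparator descriptions, "Patients who exhibit HPR defined as a PRU value of 240 units or more by VerifyNow" are randomised. The article describes no repeat reading, minimum fall or buffer. The statement "Angiography will not begin before confirmation of PRU" reads as having the result in hand, not as a second measurement. Under Sample size: "We predict that 50% of patients will exhibit HPR as determined by VerifyNow" after the loading dose.

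**The concern.** A yes/no outcome at 240 PRU counts a patient who goes from 242 to 238 as resolved and one who goes from 380 to 245 as not resolved. The size of the fall, which the objective sets out to compare and on which the sample size rests, plays no part in the primary test. With 38 patients per arm that loss of information could decide the result.

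The 50% prediction also places 240 PRU near the median of the screened patients, where they lie densest. Some patients who qualify on one high reading would be below 240 on a second reading without any drug effect. It therefore needs checking whether the shared cut-off itself does harm, or whether the loss comes from dichotomising.

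**Working it through.** **Inputs from the Protocol article:** cut-off 240 PRU at entry and outcome; 50% HPR after loading, so the median is about 240; 38 per group; inhibition 55% and 70%; two-sided 5%; power 80%; loss 20%.

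**Assumed, because the article gives none of them:** the between-patient and within-patient SD of PRU, the spread of response, and normal distributions.

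**1. The plan's own figure.** n per group = 2(1.960 + 0.842)² × (SD/15)². With SD 20.7 points this is 2 × 7.85 × 1.904 = 29.9, so 30, and 30/0.8 = 37.5, so 38. The stated figure is matched with an SD of about 20.5 to 20.7 points, but the SD is not given, so it cannot be verified. Read as two proportions, 55% against 70% would need 163 per arm. The 38 is therefore a figure for a continuous outcome.

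**2. Binary against continuous, assumed effects.** Model: true PRU normal around 240; total SD 75, within-patient SD 25; patients enter if the first reading is at least 240; 24-hour PRU = true PRU × (1 − f) + error, where f is the proportional reduction; 38 per arm. Binary HPR is tested with a pooled z test.

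| Mean reduction (SD of f) | Binary HPR | Logistic adjusted for entry PRU | ANCOVA on 24-hour PRU |
|---|---|---|---|
| 10% vs 25% (15 points) | about 67% | about 74% | about 93% |
| 20% vs 35% (20 points) | about 52% | about 57% | about 79% |

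With equal effects in the arms, the unadjusted binary test and ANCOVA each reject in about 5% of trials.

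**3. The protocol's own effect.** Apply 55% and 70% inhibition to the entry PRU with the back-solved SD of 20.7 points. HPR at 24 hours is then about 6.6% against 1.7%, which is 38 × 0.066 = 2.5 and 38 × 0.017 = 0.6 patients expected with HPR. Power is about 14% for binary HPR and 80% for ANCOVA. With 30 per arm after the planned loss it is about 9% and 69%. The Sample size section does not say whether its baseline is the entry PRU or a value before any clopidogrel, so this reading is an assumption.

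**4. Is the shared cut-off the cause?** In the model of step 2, only the outcome cut was moved, to 225, 208 or 260. Power was 64-66% against 67% at 240 (10% vs 25%), and 45-56% against 52% at 240 (20% vs 35%). Separating the two thresholds brings little or nothing.

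**5. Crossing without a drug effect.** With the cut at the median, P(second reading < 240 | first ≥ 240) = arccos(ρ)/π, where ρ = 1 − (within-patient SD)²/(total SD)².

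- 75 and 25: ρ = 1 − 625/5625 = 0.889, giving 15.1%.
- 90 and 15: ρ = 0.972, giving 7.5%.
- 60 and 40: ρ = 0.556, giving 31.3%.

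Other assumed SDs (between-patient 50-90, within-patient 5-50) widen the range to 2.5-33%. The crossing is the same in both arms.

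**The case against.** The best defence is that the trial asks whether HPR persists after reloading. The article cites a source for 240 as the HPR threshold, so using it at both times is coherent. That stands. Dichotomising is also a common, clinically motivated choice, and the planned logistic model would allow entry PRU as a covariate. That stands too, but step 2 shows that adjustment recovers only about 5 to 7 points of power and leaves a gap of about 20 points to ANCOVA.

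A reader might infer that the shared cut-off biases the result. The documents do not support this. Allocation is randomised with a concurrent clopidogrel arm, so regression to the mean is common to both arms, and the planned effect measures are between-arm relative risk and absolute risk reduction. No section plans to read a within-arm fall from 100% as drug effect.

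A reader might also infer that 8-31% noise crossing dilutes the comparison. Those figures come from SDs that the article nowhere gives. Under assumed mean falls of 20 and 60 PRU, measurement noise does reduce the HPR difference, from 0.276 to 0.216-0.266. Under 55% and 70% inhibition it leaves the difference unchanged or slightly larger (0.042 to 0.043-0.052). A second confirmatory entry reading would change the arm difference by at most 0.005 in the first of these settings.

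Finally, a repeat-reading rule could stand in the full protocol. That would not alter the point, because the binary endpoint and its analysis are fixed in this article.

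**Conclusion.** The point holds as a mismatch between a continuous aim and sample size and a binary primary outcome. The cost is power. In the scenarios run, binary HPR loses about 26 to 27 points against ANCOVA under the two assumed effects (93 − 67 and 79 − 52), and about 66 points (80 − 14) if the protocol's inhibition figures apply to the entry PRU. These sizes rest on assumed SDs, on normality and, in the last case, on one reading of an ambiguous baseline. The direction was the same in every scenario with a treatment effect.

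The shared 240 PRU threshold is not a source of bias and does not explain the loss in step 2. Its only consequence is that part of each arm's fall from 100% HPR is regression to the mean, roughly 8-31% of patients under assumed SDs.

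**What to change.** - Make the primary comparison the 24-hour PRU, analysed by ANCOVA with the qualifying pre-angiography PRU as covariate. Report the adjusted mean difference with its 95% confidence interval.
- Keep HPR (PRU ≥ 240) at 24 hours as the first secondary outcome, and name the qualifying PRU as a covariate in its logistic model.
- State that within-arm falls in HPR will not be read as drug effect.
- Reconcile the body of Table 2, which uses at least 240, with its footnote: "HPR, high platelet reactivity: more than 240 units determined via VerifyNow".

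A minimum-fall rule, for example 50 PRU, is not worth adding. It gave the same power as logistic regression adjusted for entry PRU (74% and 57% in the two scenarios of step 2), and the amount has no source in the article.

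The cost is a protocol amendment and new analysis wording. Both readings are already planned for every randomised patient, so no patients, visits or samples are added. The downside is that the headline becomes a mean PRU difference instead of an HPR proportion, which clinicians may find less direct.
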